## Abstract

ORTHOUNION is a multicentre, open, comparative, three-arm, randomized clinical trial (EudraCT number 2015-000431-32) to compare the efficacy, at one and two years, of autologous human bone marrow-derived expanded mesenchymal stromal cell (hBM-MSC) treatments versus iliac crest autograft (ICA) to enhance bone healing in patients with diaphyseal and/or metaphysodiaphyseal fracture (femur, tibia, and humerus) status of atrophic or oligotrophic nonunion (more than 9 months after the acute fracture, including recalcitrant cases after failed treatments). The primary objective is to determine if the treatment with hBM-MSCs combined with biomaterial is superior to ICA in obtaining bone healing. If confirmed, a secondary objective is set to determine if the dose of 100 × 10^6^ hBM-MSCs is noninferior to that of 200 × 10^6^ hBM-MSCs. The participants (*n* = 108) will be randomly assigned to either the experimental low dose (*n* = 36), the experimental high dose (*n* = 36), or the comparator arm (*n* = 36) using a central randomization service. The trial will be conducted in 20 clinical centres in Spain, France, Germany, and Italy under the same clinical protocol. The confirmation of superiority for the proposed ATMP in nonunions may foster the future of bone regenerative medicine in this indication. On the contrary, absence of superiority may underline its limitations in clinical use.

## 1. Introduction

Bone injuries represent an important medical problem worldwide, producing significant healthcare and societal expenditure. In Europe, complex fractures are increasing in frequency due to severe traumatic injuries, such as traffic accidents, presently with higher survivorship of polytrauma patients. While most bone injuries are capable of healing through bone regeneration by natural callus formation with standard treatments, long bone injuries may not heal, impairing the patient's life and becoming an important unmet clinical need.

Nonunions, also known as pseudarthrosis, may occur in 5% to 20% of long bone fractures that fail to heal properly, with morbidity, prolonged hospitalization, and increased expenses [1, 2]. Clinical consensus is lacking regarding the definition of nonunions [3]. Nonunions are frequently defined under the FDA guidance [4], and the absence of consolidation more than 9 months after the index fracture without evidence of progressive signs of bone healing are widely used criteria. Furthermore, nonunions are classified based on the biologic potential of bone healing [5]. Since Weber and Cech (1976), quoted by Müller et al. [6], atrophic nonunion is associated with poor vascularity and shows insufficient bone bridging to stabilize the fracture, insufficient bone biological activity in the fracture, and failure of previous treatments. These require augmentation to procure bone healing, and the current standard treatment considered as the benchmark is autologous bone grafting, obtained from the same patient at a different surgical site and transplanted to the reconstruction site.

The iliac crest holds a reservoir of spongious bone that is frequently used as a source of bone autograft, providing extracellular matrix (for osteoconduction), growth factors (modulating bone healing as per osteoinduction), and patient's cells (leading to local osteogenesis). However, major complications in 5% of the cases have been reported, including donor defect hernias, vascular injuries, sciatic nerve injury, deep infection, deep haematoma requiring transfusion, and iliac wing fracture. Minor related complications include pain at the extraction site in 5% cases, superficial haematoma or seroma or superficial infection at the extraction site in 13% cases, and ilioinguinal neuralgia in 2% cases [7]. Other limitations of iliac crest autograft (ICA) fostering research for alternatives include limited amount of available bone (particularly if previous harvesting and replacement by fibrous tissue) and limited efficacy. Although a benchmark, insufficient information about iliac crest autograft efficacy is available from the literature. When used as a control, a recent multicentric trial with 61 patients treated with autograft observed 74% radiological consolidation (45/61) by rigorous criteria (bridging in at least three of four views) at 9 months, even if only 25% of these cases were atrophic nonunions [8].

Culture-expanded autologous MSCs combined with biomaterial granules as carrier agents have been proposed as a promising technology to substitute bone autograft to augment nonunions in early feasibility studies [9, 10]. However, studies and publications vary regarding the origin of MSCs, the expansion protocol, the reproducibility and variability of the cell product, the quality of this cell product at delivery, the demographics of the treated patients, the diagnostic criteria of nonunion in the inclusion criteria, the bone healing criteria, the safety reporting, and the follow-up. Most importantly, the confirmed dose in the implanted cell product is unclear, and previous trials just declare to implant the maximum cell dose that can be generated by the available technology at the facility producing the cell expansion.

Significant preclinical work including quality assessment and standardisation of the cell product to be implanted is required before a cell product can obtain the approval for a certain trial as an investigational medicinal product (IMP) on an advanced therapy medicinal product (ATMP) under good manufacturing practices (GMP), in compliance with European regulation [11]. Besides, significant efforts in the design of a wide multicentric trial are required to confirm safety and prove efficacy, with adequate randomization against a widely accepted control, in a patient population precisely defined by specific inclusion and exclusion criteria.

As part of the EU-FP7-REBORNE project (GA 241879), the procedures of isolation, culture, and characterization of expanded human bone marrow-derived mesenchymal stromal cells (hBM-MSCs) cultured in platelet lysate (PL) were fully standardized and validated by multiple GMP production facilities in France, Italy, Germany, and Spain. The therapeutic doses obtained at release and used in the early clinical trial within the REBORNE project were 100 × 10^6^ and 200 × 10^6^ hBM-MSC cells. Cells adhered to a CE-marked granulated biphasic bioceramic and were delivered to the bone injury by open surgery after nonunion site surgical preparation. The osteogenic potential was preclinically studied both in vitro and in vivo [12, 13]. The tumorigenicity and migration of human MSCs derived from BM (tumorigenicity and biodistribution) were also preclinically studied in NOD SCID mice [14]. After validation among the GMP manufacturing centres from the four participating countries, the IMP was approved for safety and feasibility clinical trials for nonunion fractures (EudraCT number 2011-005441-13) and for avascular necrosis of femoral head (EudraCT number 2012-002010-39). No safety events related to the IMP were detected for any of these early trials. At this point, the evaluation of efficacy against the standard is still required to support the future clinical application of this technique.

MBCP+™ (Biomatlante, France) is a class III implant of wide use, CE marked (CE0123) and FDA 510(k) approved. It is a biphasic material composed of HA/*β*-TCP in a ratio of 20/80 in weight, resorbable and able to be rapidly replaced by newly formed bone [15]. The biomaterial was selected due to preclinical studies that confirmed high colonization of the biomaterial by osteogenic cells [16] and due to proven safety and efficacy of the MBCP+ alone or combined with expanded MSCs [14–16] at the selected dose [17, 18].

As a part of the EU-H2020-ORTHOUNION project (GA 733288), the global aim of this ORTHOUNION clinical trial is to overcome the major hurdle to complete the translation to clinical application. Therefore, the ORTHOUNION proposal focuses on testing the efficacy of expanded BM-hMSC in two different doses (100 and 200 × 10^6^ cells), versus iliac crest bone autograft, the currently accepted standard therapy, to biologically augment surgical treatment of long bone nonunions.

## 2. Material and Methods

### 2.1. Trial Characteristics and Design

ORTHOUNION is a multicentre, open, comparative, randomized, clinical trial with three parallel arms to evaluate the efficacy at one and two years of two doses of an ATMP against iliac bone autograft to enhance bone healing in patients with long bone nonunion (EudraCT number 2015-000431-32). A total of 108 patients will be randomly assigned to either the experimental low-dose arm, experimental high-dose arm, or the active comparator arm (ICA) with a 1 : 1 : 1 allocation using a central randomization service. The experimental low dose contains a total number of 100 × 10^6^ hBM-MSCs suspended in 5% human albumin up to a total volume of 10 mL (cell concentration of 10 × 10^6^). The experimental high dose contains a total number of 200 × 10^6^ hBM-MSCs suspended in 5% human albumin up to a total volume of 10 mL (cell concentration of 20 × 10^6^). Each experimental dose will be combined with 10 cc of the granulated biomaterial MBCP+ (Biomatlante, Nantes, France). The trial will be conducted in 20 clinical investigational sites in four European countries (France, Germany, Italy, and Spain) under the same clinical protocol and standardized surgical techniques. The cell product derived from autologous hBM-MSCs will be expanded in 4 different GMP manufacturing facilities in France (EFS Ile de France, Centre de Thérapie Cellulaire de Créteil), Germany (Institut für Klinische Transfusionsmedizin und Immungenetik Ulm Gemeinnützige GmbH (IKT Ulm), DRK-Blutspendedienst Baden-Würrtemberg–Hessen und Universitätsklinikum Ulm, Ulm), Italy (Fondazione IRCCS Ca' Granda Ospedale Maggiore Policlinico, Cell Factory “F. Calori”, Milano), and Spain (Unidad de Producción Celular UPC, Hospital Puerta de Hierro-Majadahonda, Universidad Autónoma de Madrid, Servicio de Hematología y Hemoterapia, Madrid).

### 2.2. Study Objectives

The primary objective is to determine if the combined treatment of the ATMP, *hBM-MSC + biomaterial (G2)*, is superior to the control, *iliac crest autologous graft (G1)*, to obtain radiological and clinical bone consolidation at 12 months after surgery of diaphyseal and/or metaphysodiaphyseal (femur, tibia, and humerus) atrophic or oligotrophic nonunions after a fracture (more than 9 months after the acute fracture and insufficient bone bridging to stabilize the fracture, insufficient bone biological activity in the fracture, and failure of previous treatments). The secondary objectives (SO) are the following: (SO1) to determine if the *low dose of hBM-MSC + biomaterial (G2b)* is noninferior to the *high dose of hBM-MSC + biomaterial (G2a)* to obtain radiological consolidation at 12 months after surgery of diaphyseal and/or metaphysodiaphyseal (femur, tibia, and humerus) nonunions after an unhealed fracture; (SO2) to compare the percentage of bone consolidation between the G1 and G2 treatment arms at 6 and 24 months after surgery and between the G2a and G2b treatment arms at 6, 12, and 24 months after surgery; (SO3) to compare the radiological consolidation between the G1 and G2 treatment arms and between G2a and G2b treatment arms, at baseline and 6, 12, and 24 months after surgery; (SO4) to compare pain with and without weight bearing using the Numeric Rating Scale (from 0 to 10) between the G1 and G2 treatment arms and between G2a and G2b treatment arms, at baseline and 6, 12, and 24 months after surgery; (SO5) to compare the rate of further surgical intervention at the callus site between the G1 and G2 treatment arms and between G2a and G2b treatment arms at 6, 12, and 24 months after surgery; (SO6) to compare the early and global complication rate between the G1 and G2 treatment arms and between G2a and G2b treatment arms at 6, 12, and 24 months after surgery; (SO7) to assess the safety of autologous hBM-MSCs between the G1 and G2 treatment arms at 6, 12, and 24 months after surgery; (SO8) to identify the factors associated with bone consolidation between the G1 and G2 treatment arms and between G2a and G2b treatment arms at 6, 12, and 24 months after surgery; and (SO9) to compare the physical and mental health status using the SF-36 Health Survey at baseline and 6, 12, and 24 months after surgery. Outcome measures are described in Table 1.

### 2.3. Patient Population and Evaluation

Each investigator will enroll eligible patients into the trial (after obtaining the signature of the due informed consent adapted to each national regulation) and will enter patient data into the eCRF timely throughout the study. Inclusion and exclusion criteria are shown in Table 2. During the inpatient stay, recovery, and follow-up, all participants will receive conventional treatment.

A clinical trial committee, composed by three independent expert clinicians, will review and adjudicate the primary efficacy outcomes (bone consolidation) and other collected clinical outcomes, using prespecified definitions and methods described in the Clinical Event Committee Charter. Files for adjudication will be prepared and accordingly blinded prior to adjudication.

Blood samples will be obtained for routine blood tests, serology tests (HIV-, syphilis, HBV, and HCV), and bone turnover marker tests (bone-specific alkaline phosphatase (BAP), C-terminal propeptide of type I procollagen (PICP), osteocalcin N-terminal fragment (Midtact-OC), carboxyterminal cross-linked telopeptide of type I collagen (beta-CTX), osteoprotegerin (OPG), receptor activator of nuclear factor NF-kappa B ligand (RANKL)). Flow diagrams of the trial are shown in Figures 1 and 2.

### 2.4. Treatments

The active comparator treatment (augmentation with spongious ICA) is a surgical procedure considered the standard of care, which requires the extraction of the needed spongious bone graft from the iliac crest at nonunion surgery. The experimental treatment (augmentation with autologous hBM-MSCs combined with the previously described CE-marked biphasic bioceramic) includes expansion of MSCs under GMP conditions in associated facilities. For both experimental arms (G2a and G2b), expanded autologous hBM-MSCs will be mixed in the surgical setting, immediately before implantation, with the previously described biomaterial called MBCP+, a class III, CE-marked, and FDA-approved biomaterial, provided by Biomatlante (Nantes, France) in a syringe ready to use.  Table 3 summarizes the study arms.

### 2.5. Surgical Interventions

The preparation of the nonunion site will be the same for both interventions. It will consist in the ablation of the necrotic bone fragments and intercalated fibrous tissue within the nonunion, followed by bone decortication to create a vascularized bed in which the cell composite or the autograft will be placed.

#### 2.5.1. Iliac Crest Grafting

The ICA will be obtained as per standard surgical technique. The appropriate incision after skin preparation will expose the anterior iliac crest, followed by blunt dissection. Once exposed, the surgeon will decide on the most appropriate trephines and dowels to be used to conservatively obtain the required spongious graft that will be preserved through the case in a separate container, as per standard of care. If insufficient autograft to fill and cover the nonunion is harvested, the incision and crest approach may be extended so the harvesting fulfils the bone graft needs. Usually, one single anterior iliac crest suffices to cover the autograft needs of about 10 cc for each case (similar volume to the implanted biomaterial in the experimental arm). In case of insufficient bone in the exposed iliac crest (due to previous harvesting or other surgical issues), the contralateral crest may be exceptionally required. By no means will the surgeon obtain insufficient bone autograft to complete the surgical requirements. The wound will be closed following muscle, fascia, and subcutaneous layer closure. A drain may be used if found necessary by the surgeon in charge of the case.

#### 2.5.2. Bone Marrow Mesenchymal Stem Cells + Biomaterial Implantation

First, the bone marrow will be harvested under loco-regional (epidural, spinal) or general anaesthesia. Bone marrow will be aspirated from the anterior or posterior iliac crests, after insertion of a bevelled needle (6 to 8 cm in length and 1.5 mm in internal diameter) into the spongy bone, and transferred into a 20 mL plastic syringe with 1 mL of heparin. At a given depth, the needle will be turned 45° to reorient the bevel during successive aspirations, so that the largest possible space is aspirated. After one full turn, the needle will be moved 1 cm toward the surface through the same insertion site, and aspirations will again be performed, with the needle always turned 45° after each aspiration. The marrow will be aspirated in small fractions (3–4 mL) to reduce the degree of dilution by peripheral blood. A total of 30–35 mL of bone marrow will be aspirated. If necessary, two or three perforations will be performed, through the same skin opening, into the iliac crest, with the perforations spaced approximately 2 cm from each other to avoid dilution by aspiration in the previous hole. All aspirates will be pooled in plastic bags containing an anticoagulant solution. The bone marrow will be then forwarded to the associated GMP facilities. The final product of expanded MSCs will be manufactured according to GMP rules using aseptic procedures and disposable sterile single-use supplies for all product contact steps. The whole process will be conducted in accordance with written procedures and each step will be recorded on batch. All manipulations involving the initial preparation of cells, cell culture, and cell packaging will be performed in clean rooms of appropriate class of air cleanliness. The batch production records for each lot require documentation and confirmation signatures that the procedures have been followed. Briefly, MSCs will be cultured and expanded using alpha MEM medium supplemented with PL [19]. Cells will be conditioned in a syringe for injection. The final product will consist of fresh, autologous bone marrow MSCs, expressing the markers CD90, CD73, CD105 and negative for CD14 and CD45 and HLA class II, with a 90% viability rate, at a dose of 100 × 10^6^ or 200 × 10^6^ cells (G2a and G2b) suspended in 5% human albumin up to 10 mL (the delivery contains two syringes of 5 mL each).

Secondly, the conduction of the surgery will be the same as for bone autograft, except for the implantation of the composite (hBM-MSCs + biomaterial). The mixture will be prepared in the operating room as per protocol [20] and placed in the previously prepared area to be grafted. Each 5 mL cell product syringe is mixed with 5 cc of biomaterial (1-2 mm MBCP+ granules) filling the intergranular pores. The final mixture of the biomaterial and cells has a pasty consistency and it will be preferably introduced within the gap of the nonunion. Circumferential use of the material will only be performed when the bone gap is filled.

In both cases, a stable fixation of the fracture will be required. The use of an osteosynthesis system may include static or locked nail, locked or unlocked bone plate with screws, and/or external fixator (including the Ilizarov system) when other means are not adequate. Furthermore, the surgical technique will be reevaluated postoperatively by the clinical trial committee, to confirm the predefined criteria of a satisfactory surgical procedure (stable fixation and adequate augmentation) to validate the analysis of the case as per protocol. These criteria include absence of major complications after the procedure (intraoperative fracture, deviation, inadequate reduction, or other surgical gestures or interventions, except fibular osteotomy if required for compression or reduction of a tibial nonunion), presence of sufficient biomaterial or graft (filled nonunion gap, presence of sufficient graft/material in the fracture compression side and not in the tension side), and sufficient fixation (detecting immediately after surgery what could be considered an unstable fixation or unstable nail or other suboptimal techniques).

## 3. Statistical Analysis

### 3.1. Sample Size

#### 3.1.1. Test of Superiority (Primary Endpoint) for G1 versus G2 Comparison

For an allocation 1 : 2 to test the percentage of bone consolidation between G1 and G2, the sample size of 36 in comparator arm (ICA) and 72 in experimental arm (hBM-MSC) achieve more than 80% power to detect superiority with a clinically meaningful margin of superiority of 20%, considering a 5% loss. Despite the uncertainties derived from the fact that no head-to-head comparisons have been tested in well-designed randomized clinical trials, literature data suggest that the control arm (G1) may have a rate of 74% in efficacy [8] and that it is reasonable to expect 20% superiority for the rate of responders in the experimental arm (G2a + G2b) [21, 22]. The significance level of the test will be established at the 2.5% one-sided alpha level (equivalent to 5% two-sided alpha level).

#### 3.1.2. Test of Noninferiority (Secondary Endpoint) for G2a and G2b Comparison

The sample size for the assessment of the noninferiority of G2b in front of the G2a arms will be based on the REBORNE scale. A total sample size of 72 participants with 36 in group G2a and 36 in group G2b will achieve more than 90% power to establish the noninferiority using a one-sided 2.5% alpha level. The margin of noninferiority is 10% on the ratio of means, assuming that the true ratio is 1.0 (i.e., G2a and G2b have the same effect). The coefficients of variation of both groups are assumed to be around 0.1349 based on internal data, with a mean of 0.113 and a SD of 0.815 [23].

All sample size calculations have been performed using the nQuery v7.0 validated software [24].

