**Figure 2 fig2:**
[figure not shown]
Flow diagram of the ORTHOUNION clinical trial.

**Table 1 tab1:** Outcome measure and statistical analysis table.

Objective	Outcome measure	Time points of evaluation	Statistical analysis
Principal objective: to determine if the combined treatment of the ATMP, hBM-MSC + biomaterial (G2), is superior to the control, iliac crest autologous graft (G1), to obtain radiological and clinical bone consolidation	Bone consolidation is considered achieved when meeting the three following criteria: (1) Radiographic bone bridging: new bone formation across the fracture site visible in 3/4 cortices, on at least 3/4 views (2) Clinical healing: pain less than 3 in a NRS (0 to 10) for pain during full weight bearing and without weight bearing [36] (3) No further surgical major intervention (nail replacement, plate replacement, or replacement of all components of the previous surgery)	At 12 months after surgery	Superiority (target delta of 20%). Percentages will be estimated using a log-binomial regression model including the treatment, manufacturing site, and baseline value of the REBORNE scale as covariates. If unexpectedly the model does not fit, the Poisson long-link distribution function with a robust variance estimator will be used instead.

SO1: to determine if the low dose of hBM-MSC + biomaterial (G2b) is noninferior to high dose of hBM-MSC + biomaterial (G2a) to obtain radiological consolidation	Score calculated in xR images from REBORNE radiological scale following the formula: REBORNE score = ∑(internal, external, anterior, and posterior cortical value^∗^)/(4 × number of evaluable cortices)	At 12 months after surgery	Noninferiority (target delta of 10%). A log-transformed data of the values will be used in a mix model for repeated measurements, only if the primary outcome reaches statistical significance. Differences between arms will be estimated through adjusted means, standard errors, and its 95% CI

SO2: to compare the percentage of bone consolidation between G1 versus G2 and G2a versus G2b treatment arms	As defined in the principal objective	(i) G1/G2: at 6 and 24 months after surgery (ii) G2a/G2b: at 6, 12, and 24 months after surgery	Fisher's exact test

SO3: to compare the radiological consolidation between G1 versus G2 and G2a versus G2b treatment arms	As defined in SO1	At baseline and 6, 12, and 24 months after surgery	*t*-test or Mann–Whitney test

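### The power above 90% for the low- versus high-dose noninferiority test is conditional on a significant primary result; under the plan's own gate the overall figure is about 70–75%

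*Protocol article*

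**What the plan says.** Section 3.1.2 sizes the comparison of the low dose (G2b) with the high dose (G2a) on the REBORNE radiological score. The numbers are "A total sample size of 72 participants with 36 in group G2a and 36 in group G2b", which, the section says, "will achieve more than 90% power to establish the noninferiority using a one-sided 2.5% alpha level". The assumptions are given next: "The margin of noninferiority is 10% on the ratio of means, assuming that the true ratio is 1.0", and "The coefficients of variation of both groups are assumed to be around 0.1349 based on internal data". The section mentions neither the primary test nor any loss to follow-up.

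Two other places make this comparison depend on the primary result. In Table 1, the SO1 row says the analysis is done "only if the primary outcome reaches statistical significance". The abstract, after stating the superiority objective, introduces the dose objective with "If confirmed, a secondary objective is set to determine".

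Section 3.1.1 sizes that primary test: 36 control and 72 experimental patients "achieve more than 80% power to detect superiority", for a control rate of 74%, a gain of 20 points, one-sided 2.5% alpha and a 5% loss.

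**The concern.** Under the rule in Table 1, noninferiority is established only if two things happen in the same trial: the primary test is significant, and the SO1 test then succeeds. The probability of both cannot be larger than the probability of the first. Section 3.1.1 claims only a little over 80% for the first, while Section 3.1.2 claims over 90% for the outcome that needs both. As worded, without a condition, the second claim is not a property of the procedure the trial will follow.

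What is at stake is the planning statement for one of the two comparisons that the article formally sizes. Taken at face value, it suggests less than a 10% chance of ending without a noninferiority conclusion when the doses are equivalent. Under the gate that chance is between one in four and three in ten, even if the doses are identical and the 20-point gain is real.

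**Working it through.** **Inputs.** From 3.1.2: 36 per dose arm, ratio limit 0.90, true ratio 1.0, CV 0.1349, one-sided alpha 0.025. From 3.1.1: 36 versus 72, 74% versus 94%, one-sided alpha 0.025, 5% loss. From Table 1 and the abstract: SO1 is run only after a significant primary result.

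**Step 1: reproduce the SO1 figure, without the gate.**
- Log-scale SD = √ln(1 + 0.1349²) = 0.1343.
- Standard error of the difference = 0.1343 × √(2/36) = 0.0316 to 0.0317, depending on rounding.
- Distance to the margin = −ln(0.90) = 0.1054, so the noncentrality is about 3.33.
- Power from the noncentral t with 70 df: 90.7% (normal approximation 91.4%).

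The stated figure is therefore that of the SO1 test taken alone. At 90.7% it leaves no room for the gate.

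**Step 2: reproduce the primary figure.**
- Pooled rate = (36 × 0.74 + 72 × 0.94)/108 = 0.8733.
- SE under the null = √[0.8733 × 0.1267 × (1/36 + 1/72)] = 0.0679.
- SE under the alternative = √[0.74 × 0.26/36 + 0.94 × 0.06/72] = 0.0783.
- Power = Φ[(0.20 − 1.96 × 0.0679)/0.0783] = Φ(0.855) = 80.4%.

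The exact power of the chi-square test at the same inputs is 82.0%. Both agree with the stated minimum of 80%, and both are computed with no loss.

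**Step 3: ceiling.** P(primary significant and SO1 successful) ≤ P(primary significant), which is about 80–82%. This follows from the gate alone.

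**Step 4: joint power.** When the doses are equal, as 3.1.2 assumes, pooled G2 versus G1 and G2b versus G2a are nearly independent contrasts, so the powers multiply:
- pooled formula: 0.804 × 0.907 = 72.9%;
- exact chi-square: 0.820 × 0.907 = 74.4%;
- the two stated minima: 0.80 × 0.90 = 72%.

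Independence was checked by simulating 40,000 trials per setting, with a latent correlation of 0, 0.5 or 0.9 between score and consolidation and a chi-square primary test. Joint power was 74.3%, 74.5% and 74.8%. Dividing by the simulated primary power (81.8–82.2%) returns about 91%, so the stated figure holds as a conditional one.

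**Step 5: with the 5% loss.** 36 × 0.95 = 34.2, so 34 per arm (34 versus 68 for the primary).

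| | 36 per arm | 34 per arm |
|---|---|---|
| SO1 alone | 90.7% | 89.0% |
| Primary, pooled formula | 80.4% | 78.3% |
| Primary, exact chi-square | 82.0% | 79.4% |
| Joint, pooled formula | 72.9% | 0.783 × 0.890 = 69.7% |
| Joint, exact chi-square | 74.4% | 0.794 × 0.890 = 70.7% |
| Joint, simulated | 74.3–74.8% | 70.7–71.0% |

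**Step 6: sensitivity to the primary test.** At 36 versus 72 the unpooled formula gives 72.4% and Fisher's exact test 71.9%. Joint power would then be 0.724 × 0.907 = 65.7% or 0.719 × 0.907 = 65.2%. These do not reproduce the plan's own primary figure, so they are not used for the range. In the other direction, a primary power of 85% would give 0.85 × 0.907 = 77.1%.

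**The case against.** The best defence is that no stated number is miscalculated. Section 3.1.2 is headed as a test of noninferiority and gives that test's power from its own margin, variability and sample size. Quoting per-test power for a gated secondary endpoint is common. The abstract's wording also suggests that the dose question is asked only once superiority is shown, which makes the conditional figure a relevant one.

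Most of this stands. The figure reproduces, it remains about 91% given a significant primary result, and the article nowhere calls it an overall power. What does not stand is the missing condition: 3.1.2 states a probability of establishing noninferiority, and under Table 1 that probability is lower.

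Several stronger readings are tempting but not supported:
- A reader might infer that the sample-size formula belongs to a different procedure from the analysis in Table 1. The gate decides whether the test is run; it does not change its scale, margin or alpha. A ratio of means in 3.1.2 and log-transformed scores in Table 1 agree on this point.
- A reader might infer that the article presents the dose comparison as the better-powered objective. The two percentages invite that comparison, but no passage makes it, and SO1 is labelled secondary throughout.
- A reader might fear that an untested SO1 would be taken as evidence about dose. The gate is stated twice, so an untested SO1 is explained by the primary result.
- A reader might want one exact joint figure. It depends on the primary test and the loss assumed, and no power was computed here for the covariate-adjusted log-binomial model that Table 1 specifies.

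**Conclusion.** The point holds as a missing condition on a stated power, not as an arithmetic error. The figure above 90% is right for the SO1 test once the gate has opened and with 36 evaluable patients per arm. The overall probability of establishing noninferiority is capped at the primary power, about 80%. It is about 73–75% with 36 per arm and about 70–71% after a 5% loss in both tests, roughly 15 to 20 points below the unqualified figure.

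This rests on the following assumptions:
- the plan's 74% versus 94%, and equal dose effects;
- a chi-square type primary test;
- loss handled by removing patients. Section 3.2 instead counts unknown consolidation as failure, and that variant was not computed;
- CV 0.1349. Section 3.1.2 prints it "with a mean of 0.113 and a SD of 0.815", which gives 0.815/0.113 = 7.21, or 0.113/0.815 = 0.1387 if the two are interchanged. With 0.1387, SO1 alone has 89.2% power. That inconsistency is a separate matter, but it bears on whether even the conditional figure exceeds 90%.

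The gate does not inflate the type I error, and nothing here shows that the sample size or the hierarchy must change.

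**What to change.** In Section 3.1.2, state that the power above 90% is conditional on a significant primary result and assumes 36 evaluable patients per dose arm. Add one sentence giving the overall power under the hierarchical rule as about 70–75%, and name the primary test and the loss behind it. Settle the printed mean, SD and CV before entering a more exact figure.

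Keep the sample size, the gate, the margin and the SO1 analysis as they are. The cost is a sentence or two of text and a less favourable headline figure; no additional patients are needed.
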